### Economic evaluation

The economic evaluation will estimate the cost effectiveness of the standing frame programme plus usual care, versus usual care alone. The primary perspective of the analyses will be that of the NHS and Personal Social Services (i.e. Third Party Payer), with a broader perspective to be considered in sensitivity analyses. Cost effectiveness analyses (CEA) will present an estimate of the incremental cost per unit change in the primary outcome measure (AMCA), but the primary economic analyses will be the incremental cost per QALY gained (over 36 week follow-up). The EQ-5D-5 L will be the primary economic endpoint used to estimate QALYs, applying a UK tariff [33], at final follow-up, with the MSIS-8D [29] used to estimate QALYS based on the MSIS-29, a condition specific measure. Economic analyses will estimate the resource use (e.g. standing frames, physiotherapy sessions, travel, telephone calls, social care assistance) and related cost associated with delivery of the standing frame programme, in addition to usual care, via data collected within the trial.

Data will be collected, via a self-report Resource Use Questionnaire, on participant use of health and social care services (primary, secondary and social care), and on broader aspects of participant and carer-related resource use.

Regression methods will be used to estimate incremental costs and QALYs, adjusting for baseline (cost, QALY) values, with covariates for baseline ACMA and stratification variables (baseline EDSS, geographic regions), and economic analyses will be consistent with the primary statistical analysis plan. The CEA will synthesise cost and outcome data, and explore uncertainty, to present results of the economic evaluation in a policy relevant way.

### Qualitative assessment

A qualitative approach will be used to capture and explore the “real-life” experiences of people’s participation in the standing frame programme. Purposive sampling to achieve maximum variation will be used to request 10 participants and 10 carers to keep audio diaries of their experiences of standing and using the frame. They will be asked to use an audio recorder to record their reflections and experiences on how it feels to stand, changes they are experiencing, plus any comments they wish to make throughout the intervention period. To ensure contemporaneous collection of data they will be asked to record these reflections, if possible, during each stand or as near to the completed standing period as possible.

### Statistical analysis

A full statistical analysis plan will be developed and approved by an independent statistician, prior to final database-lock. The primary statistical analysis will utilise analysis of covariance (ANCOVA), comparing AMCA scores at week 36 between allocated groups, adjusting for baseline AMCA score and the two stratification variables (baseline EDSS category and geographical region). The primary comparative analyses of all outcome measures will be on the basis of intention-to-treat (adverse events will be presented per protocol if different). Between-group differences will be presented with 95 % confidence intervals wherever possible, with the significance level for hypothesis testing set at 5 %, unless otherwise stated.

Secondary outcomes will be compared between groups in a similar way to that for the primary outcome. Comparisons of interest will be presented with 95 % confidence intervals for both unadjusted and adjusted between-group comparisons.

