### Interventions

Participants in the intervention group will be asked to stand in an Oswestry standing frame [17] for 30 min three times per week for a total of 16 weeks during a 20 week period. The Oswestry standing frame is a wooden frame, used in clinical practice, which provides support in standing whilst allowing for exercise and controlled movement.

The treating physiotherapist will teach the participant and carer safe and effective use of the standing frame over two face-to-face sessions in the participant’s home (~60 min/session). Participants will also be taught exercises and stretches to undertake in the frame. A detailed user-friendly information leaflet and digital versatile disc (DVD) will be provided to support these sessions. Further support will be provided by weekly telephone contact for four weeks, and then monthly for two months. Telephone calls will focus on facilitating individuals to set and achieve personal targets.

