### Measures of intervention adherence

A simple pre-formatted daily diary will be completed by those allocated to the standing frame programme. Either the participant or carer will record adherence with the intervention (frequency, duration, reasons for not standing), and will also have the opportunity to comment on why standing was continued or stopped. Adverse events (including new symptoms and falls) will also be recorded in the diary.

The usual care group will also be asked to complete a daily diary to capture adverse events (including new symptoms and falls).

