### Safety monitoring

Participants will be monitored for adverse events via completion of their study daily diaries and during follow-up assessments. The group receiving the intervention will also be monitored during the scheduled telephone calls with their treating physiotherapist. Physiotherapists will be asked to report all adverse events to the research team, whether or not they are thought to be related to the intervention.

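### Adverse events are assigned to an undefined per-protocol presentation which, in the usual sense of the term, could leave out participants who stopped standing because of harm

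*Protocol article*

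**What the plan says.** In the protocol article, Statistical analysis, the general rule is "The primary comparative analyses of all outcome measures will be on the basis of intention-to-treat". A parenthesis attached to that rule makes the exception: "adverse events will be presented per protocol if different". The article gives no definition of the per-protocol set and no adherence threshold. It does not say whether this display replaces one of all randomised participants or is added to it.

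Collection of harms is not restricted in this way. Under Measures of intervention adherence, the intervention arm keeps a diary: "Adverse events (including new symptoms and falls) will also be recorded in the diary". For the other arm, "The usual care group will also be asked to complete a daily diary to capture adverse events (including new symptoms and falls". Under Safety monitoring, "Physiotherapists will be asked to report all adverse events to the research team, whether or not they are thought to be related to the intervention".

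The programme against which adherence would be measured is set out under Interventions: standing "for 30 min three times per week for a total of 16 weeks during a 20 week period". The diary in that arm "will record adherence with the intervention (frequency, duration, reasons for not standing".

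**The concern.** A safety table should keep the people who were harmed. In a standing programme, an adverse event is one plausible reason for stopping or cutting down. A set restricted to those who kept to the programme is then selected partly on having tolerated it.

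The selection is also nearly one-sided. Usual care has no standing requirement to fail, so a filter on adherence thins the intervention arm and leaves the control arm almost intact. The comparison of harms then loses the protection of randomisation.

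The article itself expects non-adherence, and does not expect it to be random. The Sample size section allows for people who do not complete the programme. The Discussion hypothesises that the more disabled will adhere less and drop out more. At stake is the safety conclusion for a home programme, run largely without supervision, in severely impaired people.

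**Working it through.** **1. What the article fixes.** The only related figures are those in Sample size. Inflating 55 per group for 20% loss gives 55 / (1 − 0.20) = 68.75, so 69 per group and 138 in all, which the article rounds to 140. That agrees with the stated figures, and at 1:1 it means 70 per arm. The 20% is an allowance for loss to follow-up, not a rate of stopping standing. The article gives no stopping rate and no adverse event rate.

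**2. Three readings of the parenthesis.**
- *Exclusion of non-adherers*, the usual meaning: people who stopped, including those who stopped because of harm, are left out.
- *Grouping by treatment actually received*: nobody is dropped for stopping, and this problem does not arise.
- *An extra display beside one of all randomised participants*: nothing is hidden, provided the full display is also given.

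**3. Size under the first reading (all rates assumed).** Let s be the share of the intervention arm that stops, p_a the event risk in adherers and p_s the event risk in stoppers.
- Risk in all randomised to the programme: s × p_s + (1 − s) × p_a
- Risk shown per protocol: p_a
- Understatement: s × (p_s − p_a)

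Worked case with s = 20%, p_a = 20% and p_s = 50%: 0.2 × 0.50 + 0.8 × 0.20 = 0.26. The table of all 70 would show 26%. A table of the 56 adherers would show 20%, which is 6 points lower.

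Understatement in percentage points, with p_a = 20% throughout (a negative value means the per-protocol figure is too high):

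| Risk in stoppers | s = 10% | s = 20% | s = 30% | s = 40% |
|---|---|---|---|---|
| 50% | 3 | 6 | 9 | 12 |
| 30% | 1 | 2 | 3 | 4 |
| 20% | 0 | 0 | 0 | 0 |
| 10% | −1 | −2 | −3 | −4 |

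If the usual-care figure is unaffected, the whole of this error passes into the between-arm risk difference.

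**4. Falls.** Secondary outcome measures lists falls frequency, taken from the daily diary, as a key clinical outcome. The general rule in Statistical analysis therefore puts it on intention-to-treat. Measures of intervention adherence counts falls among the adverse events in both arms, so the parenthesis sends the same diary entries to a per-protocol presentation. Wherever the two sets differ, whatever per protocol means, one data source could yield two between-group comparisons. The article does not say which leads.

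**The case against.** The strongest reply is that the article does not say anyone will be excluded. The parenthesis is short, the set is undefined, and analysis-set definitions usually belong in the full statistical analysis plan, which the article promises before final database lock and which is not shown here. The authors may have meant treatment received, or an additional table. This stands. It means that the absence of a definition is not itself the fault. The fault is the stated choice of label, which in ordinary usage names the unsuitable option and which the analysis plan would inherit.

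Several safeguards also remain. Falls and spasm frequency are secondary outcomes and so stay on intention-to-treat. All adverse events are collected, related or not. The Trial Steering Committee monitors adverse events and its chair receives quarterly updates, with no per-protocol filter stated. These points limit the damage, but they do not settle which participants appear in the published safety table.

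Nor is the filter strictly confined to one arm: a usual-care participant who began using a frame could also count as a deviator. Time lost to illness or holidays is allowed for within the 20 weeks, so reduced standing need not be a deviation. Both points are fair, which is why the asymmetry is described as near rather than complete.

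A reader might infer that the plan does drop those harmed and will make the programme look safer than it is. The documents do not support that. They name no exclusion, and recording "reasons for not standing" shows only that reasons are captured, not that those people are removed. The direction of any bias depends on event risk in stoppers, which is not given. Stoppers have less exposure to standing and could have fewer events.

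**Conclusion.** The point holds in conditional form. The article makes a definite statement that adverse events may be presented on a set other than intention-to-treat. It uses a term whose usual meaning excludes non-adherers to a requirement that falls essentially on the intervention arm. If that meaning applies, harms that led to stopping could be lost and risk understated.

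The size is not known. The range in the working, from 12 points too low to 4 points too high, rests wholly on assumed rates. The 6-point case is one scenario, not an estimate. Under the treatment-received reading the bias does not arise. The double treatment of falls does not depend on the excluding reading. The primary analysis, sample size and significance level are unaffected. The wording should be settled before database lock because it governs the whole adverse event comparison.

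**What to change.** Replace the parenthesis in Statistical analysis with: *Adverse events will be presented for all randomised participants by allocated group; where different, a supplementary table by treatment actually received (any frame use versus none) will be added, with no exclusion for adherence.*

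If a per-protocol display of adverse events is still wanted, define the set in the statistical analysis plan and label the display as supplementary. With allocated group as the leading presentation, falls reported as an outcome and falls reported as adverse events rest on the same population.

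The cost is one sentence and possibly one extra table. No further data are needed for the main table, since events are already collected in both arms.

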### Subgroup analyses

Exploratory analyses of the possible interaction between baseline EDSS and allocated group will be undertaken, to explore whether any difference between the allocated groups is modified by baseline EDSS category (≤7.0 vs ≥7.5).

### Qualitative analysis

Participants’ stories will be gathered, analysed and reported using narrative methodology [34]. The texts from audio recordings will be left whole, crafted into a story, and not fractured into themes, as an attempt to capture the immediate impact of standing, and to form a chronological record of the person’s experience. This promotes a contextual and holistic account; providing stories that are intended to resonate with people with MS, their families and professionals. By reading these stories the aim is to encourage the reader to reflect on their own situation gaining insight into their own experience as a person standing and living with MS, assisting a person to stand or as a professional.

### Data management, audit and monitoring

Data will be recorded on study specific data collection forms by the research therapists. Completed forms will be entered onto a password-protected customised database, developed by the Peninsula CTU. All data will be double entered and compared for discrepancies. Discrepant data will be verified using the original paper data sheets.

Participants’ anonymity will be maintained on all documents. Data will be collected and stored in accordance with the Data Protection Act 1998, and will be accessible for the purposes of monitoring, auditing, or at the request of the regulatory agency.

### Trial management committees

There are two trial management groups involved in the set up and management of this trial: the Trial Management Group (TMG) and the Trial Steering Committee (TCS).

The TMG comprises 10 individuals involved in the study design and protocol development. The group will meet approximately monthly to oversee the general management of the day to day running of the trial and release the trial results and publications. Closely involved with the sponsors, most members are co-investigators on this study. In contrast the decisions made by the TSC are independent of the sponsors and investigators. The TSC, which meets annually, comprises eight individuals, with majority independent representation (chair, external statistician, member of MS Society and two independent lay members. In addition the chair of the TSC will receive a quarterly update of the adverse events, and a telephone conference / additional face-to-face meeting will be instigated by the Chair or the Chief Investigator should any issues need to be discussed.

The role of the TSC is to oversee the conduct of the trial, including for instance monitoring adverse events, recruitment and attrition rates, the project timeline and finances.

### Ethics

The trial will be conducted in accordance with the ethical principles that have their origin in the Declaration of Helsinki, 1996; the principles of Good Clinical Practice, and the Department of Health Research Governance Framework for Health and Social Care, 2005. The study protocol, participant information and enrolment procedures were assessed and approved through the National Research Ethics Scheme (NRES Committee South West – Frenchay, REC ref no. 15/SW/0088) and management permissions gained from the Research and Development Departments of the eight participating centres in accordance with NHS research governance arrangements. Any amendments to the protocol will be reported to, and approved via NRES.

### Dissemination plan

We will target users, clinicians, researchers, organisations developing clinical guidelines and NHS decision makers. On completion of the trial, the full study report will be accessible on the study web-site page, as will the full protocol. This protocol (Version 3.0, dated 5.2.2015) has been published in line with SPRIT Guidelines [35]. Similarly CONSORT (Consolidated Standards of Reporting Trials) [36] and The Template for Intervention Description and Replication (TiDIER) Guidelines [37] will be reviewed prior to submitting future publications of the trial results to high quality journals. Authorship of intended articles will be by the study team; professional writers will not be used. Results will be presented at national and international conferences to ensure dissemination to academics and those responsible for service delivery. In addition results will be disseminated through the newsletters of MS organisations and via talks to their local support groups. If proven effective, the training materials (treatment manual, instructional video recordings, case scenarios) will be made freely available via the study website, with the aim of optimising roll out. Extracts from the audio recordings will also be used as educational and decision making tools for use by both people with MS and therapists involved in their care. All participants, who consent to receiving notifications, will be notified in writing of trial outcomes.

## Discussion

Preliminary evidence from two small-scale studies suggests that the use of standing frames in the home may improve physical and psychological well-being in people with MS [16, 17]. This protocol describes the first large-scale trial to evaluate the use of the standing frame in this way. It is important to determine definitively whether such a programme is clinically and cost effective so that people affected by MS, clinicians, commissioners and policy makers can make informed evidence-based decisions regarding the use of this intervention.

Some of the choices in the study design warrant discussion. First we discuss why our inclusion criteria were confined to those individuals with progressive disease. This is for two main reasons: the lack of disease-modifying drugs for progressive MS which means that management is aimed solely at minimising symptoms and, if possible, improving function; and the paucity of studies devoted to improving mobility in people with progressive MS [38]. As a consequence there are few proven interventions for these people. By testing the use of standing frames in a multi-centre randomised controlled trial, we may be able to identify a successful and cost effective intervention. In doing so, the results have the potential to change clinical practice and optimise supported self-management within a population that receive little attention, yet are severely affected by their condition.

The second relevant issue is the stratification by region and baseline disability level (as determined by the EDSS ≤7.0 or ≥7.5). We stratified by region (South West England versus East Anglia) because of possible differences in terms of usual care provided. Stratification by disability level was included because of the potential differences in ability of participants to adhere to the intervention, and respond to it. We hypothesise that those with higher levels of disability will have lower levels of adherence and be at higher risk of drop out of the study. Furthermore, more severely impaired participants may utilise greater levels of health and social service provision which may bias the cost effectiveness and cost-utility analyses.

Third, the dose (frequency and intensity) of the self-management standing intervention and the time frame over which this was increased was informed by a combination of scientific and anecdotal evidence. The standing duration of 20 weeks factors in up to four weeks for individuals to become gradually re-accustomed to an upright position and to steadily achieve the desired intensity of standing (three times a week for 30 min per session over 16 weeks) which was based on previous studies [16, 17]. In doing so, we hope that it will minimise fatigue, and allow for time when the participant is unable to use the frame (illness, holidays, etc.), as highlighted by our user discussion groups.

Fourth, a practical issue that we considered was which of the various commercially available standing frames we would utilise for this study. The Oswestry Standing Frame was chosen because: (a) it is commonly used within both the National Health Service, the charitable sector (e.g. MS Centres), and within undergraduate physiotherapy teaching, hence minimising the training requirements for clinicians; (b) it is both durable and recyclable, and hence can be recirculated for use within the health service thereby enhancing sustainability; (c) it is relatively lightweight (the frame can easily be pushed across a floor by one person) which makes it easy to move into a position for standing in the home and then returned to a storage part of the room when not in use; (d) it is used within current clinical practice in a range of conditions (e.g. stroke, spinal cord injury, cerebral palsy) and hence, should the results of this trial be negative, then it could continue to be recycled for use within the health service; (e) it is one of the cheapest frames on the market, and finally (e) it is wooden and hence perceived by some patients as “more like a piece of furniture”, which is an important consideration given that these frames will be used within people’s homes.

### Trial status

Recruitment started in September 2015 and is ongoing (49 participants recruited as of 21st March 2016).

### Ethics approval and consent to participate

The study protocol, participant information and enrolment procedures were assessed and approved through the National Research Ethics Scheme (NRES Committee South West – Frenchay, REC ref no. 15/SW/0088) and management permissions gained from the Research and Development Departments of the eight participating centres in accordance with NHS research governance arrangements. Any amendments to the protocol will be reported to, and approved via NRES.

### Availability of data and material

Data generated as a result of this study, and on which the conclusions of future manuscripts will be relied, will be presented in the main paper or additional supporting files.

## Abbreviations

AMCA: Amended Motor Club Assessment
ANCOVA: analysis of covariance
CEA: cost effectiveness analyses
CONSORT: Consolidated Standards of Reporting Trials
CTU: Clinical Trials Unit
DVD: digital versatile disc
SUMS: Standing Up in Multiple Sclerosis
EDSS: Expanded Disability Status Scale
HRQoL: Health-related quality-of-life
MSIS: Multiple Sclerosis Impact Scale
NHS: national health service
NRES: National Research Ethics Scheme
QALY: quality adjusted life year
RCTs: randomised controlled trials
SUMS: multiple sclerosis
TCS: trial steering committee
TiDIER: Template for Intervention Description and Replication
TMG: trial management group
UK: United Kingdom
UKCRC: United Kingdom clinical research collaboration
